# Pilot randomised controlled trial of protective socks against usual care to reduce skin tears in high risk people “STOPCUTS”: study protocol

**DOI:** 10.1186/s40814-015-0005-3

**Published:** 2015-04-01

**Keywords:** Skin tears, Pre-tibial lacerations, Prevention, Protective socks, Dermatuff

## Abstract

**Background:**

Skin tears are traumatic injuries occurring mostly on the extremities due to shearing and friction forces that separate the epidermis and the dermis from underlying tissues. They are common and occur mostly in older adults and those taking medications that compromise skin integrity. Pretibial skin tears can develop into leg ulcers, which require lengthy, expensive treatment to heal. Traumatic injuries are the second most common type of wounds after pressure ulcers in care homes and are the commonest reason for older adults to require the attention of a community nurse. Common causes of skin tear injuries are bumping into furniture and other obstacles, using mobility aids, transfer to/from wheelchairs, getting in and out of bed and falls. No effective preventative measures currently exist but knee-length, protective socks are now available that contain impact-resistant Kevlar fibres (of the type used in stab-proof vests) and cushioning layers underneath.

**Methods/design:**

In this pilot parallel group, randomised controlled trial, 90 people at risk of skin-tear injury will be randomised with equal allocation to receive the intervention or usual care. They will be recruited from care homes and from the community via general practices and a research volunteer database. Pilot outcomes include recruitment, eligibility, attrition, ascertainment of injuries and completion of outcome measures. Acceptability of the intervention and of study participation will be explored using semi-structured interviews. The proposed primary outcome for the future definitive trial is skin tear-free days. Secondary outcomes are skin tear severity, health status, specific skin-tears quality of life, capability and fear of falling, measured at baseline and the end of the study and in the event of a skin tear.

**Discussion:**

The results of this study will be used to inform the development and design of a future randomised controlled trial to assess the effectiveness and cost-effectiveness of a unique and innovative approach to skin tear prevention.

Approval was granted by the NRES - Cornwall and Plymouth Research Ethics Committee (13/SW/013). Dissemination will include publication of quantitative and qualitative findings, and experience of public involvement in peer-reviewed journals.

**Trial registration:**

Current Controlled Trials: ISRCTN96565376

## Background

Skin tears are traumatic wounds involving a piece of skin of varying size being peeled away from underlying tissues either completely or leaving a partial or intact skin flap. They often occur as a result of rubbing, an abrasion or a glancing blow to an arm or leg (i.e. from a fall or being struck or poked obliquely). The most commonly cited definition of skin tear is that of Payne and Martin: “A skin tear is a traumatic injury occurring principally on the extremities of older adults as a result of shearing or friction forces which separate the epidermis from the dermis (partial thickness wound) or which separate both the epidermis and the dermis from underlying structures (full-thickness wound)” [1]. These are common injuries [2-6]. Some prevalence data comes from America [7-10] and more recently from Japan where point prevalence was 3.9% amongst 410 patients in long-term care [11] and Australia where two elderly care rehabilitation units reported 10% [12]. A non-systematic review [9] reported skin tear incidence between 2.23% and 41.5% and prevalence between 6.6% and 23.5% in US care homes. In Pennsylvania, skin tear reporting became mandatory for healthcare facilities in 2004 [13], where 88.2% of the 2,807 skin tears were in patients aged over 65 years. Fourteen percent of an American 120-bed nursing home population sustained a skin tear per month with an average of 2.67 tears per resident [14]. A recent wound point prevalence audit undertaken in North Devon [15] in 16 care homes revealed 195 wounds amongst 115 of 458 residents (25%). Traumatic injuries were the second most common wound type (37, 19%) after pressure ulcers (87, 45%).

Several changes occur in the skin that increase its susceptibility to traumatic injury [16,17]. These changes are due to intrinsic ageing and cumulative extrinsic factors such as photoageing and polypharmacy. They include vascular atrophy and deterioration of the dermis as collagen and elastin fibres become more sparse and disordered, holding the skin layers together less tightly [18]. Older patients may have also taken oral steroids that compromise skin integrity and tensile strength and cause wounds to heal more slowly [19-22]. They may also be less aware that an injury has occurred due to decreased pain perception and tactile sensitivity, including diabetic neuropathy [23]. Fragile skin is most common in people aged over 75 years. There were 10 million people in this age group in the UK in 2012, estimated to increase to 17 million in 2032 [24]. Skin tears are unpleasant and provoke anxiety. They can take a long time to heal and are prone to infections. Whilst arm injuries are more common, leg injuries may develop into leg ulcers, which may require lengthy, expensive treatment [25]. Typical causes of injury leading to skin tears include wheelchair use, bumping into obstacles, transfers and falls. There are best practice guidelines for treatment and preventing infections and ulcers [26]. Prevention includes staff education, regular assessment, ensuring clothing does not rub, removing obstacles and moisturising the skin [9,27,28].

The novel, knee-length protective socks have a leg section woven from Kevlar [29] and elasticated nylon using the “terry sandwich” method. This gives a flat, slightly ribbed and stretchy, outer woven base which provides a tough, cut and abrasion-resistant exterior. There is a mesh of loops on the inside to provide a cushioning and impact resistant inner layer. The stretchiness is sufficient to fit a range of leg diameters within each size without applying excess pressure, and the socks are held up with a light elastane soft top band. The foot of the socks is manufactured from cotton as laceration protection is not usually required for the feet. Compression hosiery could be worn underneath if required as the socks are not designed to offer any compression themselves. Patients requiring such hosiery are excluded from this study, however, as this may confound any protective effects.

Apart from small-scale, uncontrolled testing during development, there has been no trial of the effectiveness and cost-effectiveness of this unique and innovative approach to skin tear prevention. This study will test the feasibility of running such a trial by addressing areas of uncertainty within the study protocol.

## Method/design

The study is an open, parallel group, randomised controlled study in which participants are randomised to one of two groups; the intervention group will wear the protective socks on a daily basis for a period of 16 weeks whilst the participants in the control group will wear their usual clothing. See Figure 1 for the patient flow diagram and Table 1 for the study schedule. The study is conducted in Devon, UK and aims to recruit 90 participants, 45 in each arm. The main eligibility criteria for participants are presented in Table 2. Experiences of using the socks and/or taking part in the study will be captured through semi-structured interviews with a purposive sample of participants from both the intervention and control arms of the study.

**Figure 1 Fig1:**
[figure not shown]
Participant pathway diagram (taken from the Participant Information Sheet).

**Table 1 Tab1:** Tabulated study schedule

Study procedure	Set up (Visit 1)	Baseline/Study Day 0 (Visit 2)	Study Day 1 (the day after consent)	Upon new injury	Weekly* for 16 weeks	Study Day 112	Qualitative data collection
Identify potentially eligible participants	X						
Provide Participant Information Sheet	X						
Informed consent		X					
Collection of baseline information		X					
EQ5D-5 L questionnaire		X		X^c^		X	
ICECAP-O questionnaire		X		X^c^		X	
FES-I (short) questionnaire		X		X^c^		X	
Randomisation		X					
Provision of socks (intervention arm only)		X					
Wearing of socks (intervention arm only)			X --------------------------------- > X				
Completion of participant diary (intervention arm only)			X --------------------------------- > X				
Photograph wound				X^b^			
Measurement of wound				X^b^			
Wound scoring				X^b^			
Cardiff wound impact schedule^a^				X^c^		X^d^	
Adverse event recording			X --------------------------------- > X^e^				
Research nurse to visit care home for progress checks					X		
Patient interviews							X
Focus groups							X

^*^Regular contact (visit or telephone), approximately weekly.

^a^Completed only by participants who experienced one or more skin tear injuries during their study participation.

^b^Performed within one working day following injury.

^c^Performed seven days post-injury.

^d^Completed on Day 112 by all participants who experienced skin tear injury during the study. In addition, participants who incur an injury during week 16 (Day 106 to 112 inclusive), will also complete the questionnaire seven days post-injury.

^e^Day 112 or Day 112 + 1 to 7 days if a skin tear injury occurs during week 16.

**Table 2 Tab2:** Main eligibility criteria (inclusion and exclusion criteria)

Inclusion criteria	Exclusion criteria
Resident in a care home or living in the community and at high risk of skin tears.	Not competent to give informed consent in the opinion of the recruiting nurse.
Aged 65 years or older.	Bedbound.
Ambulatory and/or wheelchair user able to take part in daily activities within a care home or in the community.	Being treated for current lacerations or ulcers on their legs.
	Participant likely to use graduated compression stockings or similar during the intervention period.

The participants will be recruited primarily from Care Quality Commission registered care homes. Residents of care homes are widely recognised to be an under-researched population and at high risk of suffering skin tears. Depending on recruitment rate of both homes and participants, up to 45 homes are expected to take part. In order to augment recruitment, patients in the community will also be invited to participate. For logistical reasons, in order to maximise efficiency in terms of research nurse resource, recruitment efforts will be focused on three geographical areas successively (Exeter, Exmouth/Sidmouth and Mid Devon, roughly representing urban, coastal and rural situations, respectively).

### Research question

The research question for the eventual definitive trial will be “Are protective, Kevlar-woven socks (‘Dermatuff’) when compared with care as usual, effective and cost-effective in providing lower leg skin protection in people at risk of suffering skin tears in terms of their incidence and severity?” The research question for this pilot is: “Is it feasible to conduct a trial of ‘Dermatuff’ protective socks compared to care as usual in people at risk of suffering skin tears?”

### Trial objectives

This pilot study is intended to pave the way for a definitive randomised controlled trial assessing the effectiveness and cost-effectiveness of the new socks in protecting the lower legs. The aim of this pilot study is to provide the necessary information for the planning of the future trial. It will test the feasibility of running such a trial and provide estimates of recruitment (care homes and residents, and patients in primary care), trial attrition, completion of questionnaire-based quality of life measures, baseline scores and standard deviations of those measures in this population. It will test the feasibility of gathering data on skin tears occurring in care homes and in the community by research nurses. It will assess the acceptability of using the protective socks and also of participating in the trial. It will provide useful information about the distribution of the variables to inform the sample size calculation for a larger trial. It will also provide an estimate of the impact of any contamination (during subsequent interviews).

Specific objectives of this pilot study are therefore:To examine the feasibility and acceptability of the research design, methods and outcome measures prior to a definitive randomised trial.To assess the processes for capturing outcome data.To refine the intervention if appropriate through qualitative work on acceptability.To determine recruitment and retention rates (at care home and resident or community participant level) to a randomised trial.To estimate concordance with the intervention.To estimate attrition rates from the study.To consider outcome measures which are important and appropriate for participants for use in the full trial.To evaluate the appropriateness of two systems of skin tear classification as outcome measures for the main trial.To estimate rates of questionnaire completion.To obtain baseline estimates of scores on the proposed outcome measures in this clinical population.To estimate the variability of outcomes to inform the sample size of the definitive trial.To calculate the sample size required for a definitive trial.To help establish the eligibility criteria for the future definitive trial (primary care patients, care homes and residents).To estimate the ability to obtain cost and effectiveness measures.To refine the clinical protocol for the use of protective socks in the full trial.To gain further understanding of the practicalities of running a trial in this population.To obtain feedback from nursing homes regarding the acceptability of the study.

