#### Procedure in the event of a skin tear injury

Care home staff or the community participant themselves will be asked to contact the research nurse by telephone immediately on becoming aware of an injury (i.e. as soon as possible on the day of the injury or the following morning in the case of an overnight injury). The research nurse will visit the resident or patient as soon as practicable (within 1 to 2 working days) of being contacted in order to collect the following:Date and approximate time of injury.Brief description of injury cause.Type of lower leg clothing and footwear worn at the time of injury (including whether protective socks were in place for participants in the intervention group).Size of injury (length, width and total area using a grid tracing method).Category of injury using the Payne-Martin and STAR classifications (as described in Appendix).A photograph of the injury.Information relating to the initial management of the injury (dressing type, referral to external healthcare professional such as GP, district nurse and hospital emergency department).

The research nurse will inspect the wound for signs of infection and will also check that the injury has been noted in the care home records (in the case of care home participants). Injured participants will complete outcome measure questionnaires 7 days post-injury.

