#### Qualitative interviews and focus groups

Semi-structured qualitative interviews with ten participants from each arm of the study will be conducted at the end of the follow-up period by an independent researcher. These will include a range of participants with varying degrees of mobility across the areas. Experiences of using the protective socks, their acceptability and/or taking part in the study will be captured. The participants will be selected using purposive sampling informed by research nurse data on their clinical progress with regard to skin tears, perceived protection from knocks and falls, withdrawals, adverse events and any problems with the skin-tear and/or questionnaire data collection process. Interviews will be digitally recorded and transcribed with the main themes identified using content analysis.

Two focus groups will be held to explore the usefulness of the protective socks. These will include professionals from the Tissue Viability Service and care home staff with experience of participants assigned to the intervention arm of the study. Holding two focus groups provides easy access for staff of care homes across the large geographical area of the pilot trial.

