One possible weakness of the pilot study design is the potential for contamination because the socks are commercially available on the Internet. Participants and/or their relatives or carers will know of the existence of Dermatuff socks, having read about them in the study Participant Information Sheet. It would not be difficult to obtain some socks for themselves if they have originally been assigned to the control group and decide that they need some. In primary care recruitment, it is also possible that GPs may recommend Dermatuff socks to their patients in the control group, hence contaminating the sample. Any contamination that occurs in this pilot will be recorded, and the information will be used in the planning of a future trial. Cluster randomisation would not prevent this direct contamination, but it might minimise the “indirect contamination” caused by control group participants seeing intervention group participants wearing the socks, and altering their own behaviour to better protect their legs — by perhaps being more careful how they move around or taking other protective measures — such as wearing their own leg-wear more often.

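### The interviews named as the source of the contamination estimate cover only ten purposively chosen controls and cannot show how common contamination is; one fixed question to every control at Day 112 could

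*Protocol article*

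**What the plan says.** The protocol article lists a contamination estimate among the things the pilot will deliver (Trial objectives): "It will also provide an estimate of the impact of any contamination (during subsequent interviews". Qualitative interviews and focus groups fixes the size and timing of the participant interviews: "Semi-structured qualitative interviews with ten participants from each arm of the study will be conducted at the end of the follow-up period". Selection is not random: "The participants will be selected using purposive sampling informed by research nurse data on their clinical progress with regard to skin tears", together with perceived protection, withdrawals, adverse events and data-collection problems, and a spread of mobility and area. The transcripts go to content analysis. Contamination is neither a listed selection factor nor a listed topic.

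The Discussion describes the routes. The socks are on open sale, every participant has read about them, GPs might recommend them, and controls might change their behaviour after seeing others wear them. It then commits: "Any contamination that occurs in this pilot will be recorded", for use in planning the later trial. No form, timing or question is given.

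Elsewhere, Table 1 restricts the daily record to one arm ("Completion of participant diary (intervention arm only") and has no contamination item. The list of pilot outcomes does not include contamination. At an injury, lower-leg clothing is recorded for any injured participant, with a parenthesis, "including whether protective socks were in place for participants in the intervention group". Method/design "aims to recruit 90 participants, 45 in each arm".

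**The concern.** The article pairs a stated aim with a stated method that does not fit it. The impact of contamination on a future trial depends on how many controls obtain or wear the socks. Ten interviewees chosen for variety of experience can show how and why this happens. They cannot give a proportion for an arm of about 45.

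Calculating the definitive sample size is one of the pilot's specific objectives. Sock use among controls narrows the contrast between the arms, so a trial sized without allowing for it would be too small. If the pilot ends with an unknown control-arm proportion, the allowance will be a guess, and unnoticed use would be counted as usual care.

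**Working it through.** **Plan's own figure.** The article gives no contamination rate and no target precision, so there is nothing to reproduce.

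**Inputs.**
- Controls interviewed: 10 (Qualitative interviews and focus groups).
- Control arm: 45 (Method/design).
- Controls answering a question put to all: 45 at best. With 20% loss, an assumption that borrows the dropout percentage under Sample size, 45 × 0.8 = 36.

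**Step 1: what each control-arm source covers.**

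| Source | Controls covered |
|---|---|
| Interviews | 10, purposive |
| Daily diary | none |
| Leg-wear at injury | injured controls only |
| Regular nurse contact, about weekly | all, but no contamination item is shown |
| Day 112 questionnaires | all, but no contamination item is shown |

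**Step 2: precision if the ten were a random sample.** With no users among n, the exact two-sided 95% upper limit is 1 − 0.025^(1/n).
- n = 10: 1 − 0.025^(1/10) = 30.8%
- n = 36: 1 − 0.025^(1/36) = 9.7%
- n = 45: 1 − 0.025^(1/45) = 7.9%

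With about 20% users, the Clopper-Pearson intervals are:
- 2/10: 2.5 to 55.6%
- 7/36: 8.2 to 36.0%
- 9/45: 9.6 to 34.6%

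**Step 3: chance of seeing nothing.** If K of 45 controls used the socks, a random ten would include none of them with hypergeometric probability C(45−K, 10)/C(45, 10).
- K = 2: 0.60
- K = 5 (11% of the arm): 0.27

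**Step 4: the sample is purposive.** The limits in Step 2 for n = 10 assume random selection, so they do not apply to these interviews. Without any sampling assumption, 0 of 10 is compatible with anything from 0/45 to 35/45, that is 0 to 78%.

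**Step 5: consequence for the definitive trial.** Assume that a contaminated control gets the full sock benefit and that the variance is unchanged. A proportion c of such controls shrinks the difference to (1 − c) of its value, and the sample grows by 1/(1 − c)².
- c = 0: 1.0
- c = 7.9%: 1/0.921² = 1.18
- c = 10%: 1/0.90² = 1.23
- c = 20%: 1/0.80² = 1.56
- c = 31%: 1/0.69² = 2.10

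None of 10 therefore leaves a range of 1.0 to 2.1 even on the favourable random-sample reading. None of 36 to 45 leaves about 1.0 to 1.2.

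**The case against.** The strongest reply is that this is a condensed article. The Discussion commits to recording any contamination in the whole pilot, nurses are in regular contact with everyone, and the case report forms are not shown, so a suitable question may already exist. That stands as a caution. It rules out the inference, which a reader might draw, that most controls are never asked about sock use: the article does not say so. It does not remove the point, because the one method the article names is the interviews. If a form already covers this, Trial objectives names the wrong source and needs correcting.

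A second reply is that the article promises an impact, not a rate, and that interviews suit the exploration of changed behaviour. The second half is right. On the first, an impact on sample size cannot be quantified without a rate.

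Third, the injury record takes leg-wear in both arms, so socks on an injured control could be captured there. That is correct, and it confines the gap to uninjured controls and to use at times other than an injury.

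Fourth, asking controls at every weekly contact could itself prompt the behaviour change that the Discussion describes. This also stands, and it is why the question belongs at the end of follow-up.

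**Conclusion.** The concern holds in a limited form. As stated, the interviews cannot quantify contamination in the control arm, and no other source described in the article fills the gap for uninjured controls. The validity of the pilot is not threatened; one of its planning aims is out of reach as written.

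The size rests on assumptions. The 31% limit treats the ten as a random sample, which flatters the interviews. The 8 to 10% limits need 36 to 45 answers and no observed use. The growth of 1.0 to 2.1 times, against 1.0 to 1.2, requires contaminated controls to receive the full sock benefit; partial or occasional use would matter less.

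Two stronger readings are not supported. A reader might infer that contamination is the principal weakness of the design, but the Discussion presents it as one possible weakness. A reader might also infer that the estimate will decide between individual and cluster randomisation. The Discussion says that clustering would not prevent controls from obtaining socks directly and might only lessen indirect effects. The figures above concern direct sock use, so they bear on sample size and not on that choice.

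**What to change.** 1. At Day 112, or at withdrawal where the participant is willing, put a fixed item to every control, or to care staff on their behalf: did they obtain or wear the protective socks during the study, and did they change their usual leg-wear? Ask before the end-of-study pair is offered to controls. The Withdrawal and dropout section bars further data after loss of capacity, so those controls should be reported as missing.
2. Have nurses log any sock use by controls that they notice at the existing regular contacts, without prompting.
3. State that the leg-wear item at injury also identifies protective socks worn by injured controls.
4. Report the control-arm proportion with its denominator and an exact 95% confidence interval.
5. Reword Trial objectives so that the proportion comes from these items and the interviews supply reasons and indirect contamination.

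The cost is one or two extra items at an assessment that already takes place, and some recall error over 16 weeks. Asking at the end avoids prompting controls during follow-up.
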